## Abstract

**Introduction:**

Binge eating disorder (BED) is a common mental disorder, closely associated with obesity. Existing treatments are only moderately effective with high relapse rates, necessitating novel interventions. This paper describes the rationale for, and protocol of, a feasibility randomised controlled trial (RCT), evaluating the combination of transcranial direct current stimulation (tDCS) and a computerised cognitive training, namely approach bias modification training (ABM), in patients with BED who are overweight or obese. The aim of this trial is to obtain information that will guide decision-making and protocol development in relation to a future large-scale RCT of combined tDCS+ABM treatment in this group of patients, and also to assess the preliminary efficacy of this intervention.

**Methods and analysis:**

66 participants with Diagnostic and Statistical Manual-5 diagnosis of BED and a body mass index (BMI) of ≥25 kg/m^2^ will be randomly allocated to one of three groups: ABM+real tDCS; ABM+sham tDCS or a wait-list control group. Participants in both intervention groups will receive six sessions of ABM+real/sham tDCS over 3 weeks; engaging in the ABM task while simultaneously receiving bilateral tDCS to the dorsolateral prefrontal cortex. ABM is based on an implicit learning paradigm in which participants are trained to enact an avoidance behaviour in response to visual food cues. Assessments will be conducted at baseline, post-treatment (3 weeks) and follow-up (7 weeks post-randomisation). Feasibility outcomes assess recruitment and retention rates, acceptability of random allocation, blinding success (allocation concealment), completion of treatment sessions and research assessments. Other outcomes include eating disorder psychopathology and related neurocognitive outcomes (ie, delay of gratification and inhibitory control), BMI, other psychopathology (ie, mood), approach bias towards food and surrogate endpoints (ie, food cue reactivity, trait food craving and food intake).

**Ethics and dissemination:**

This study has been approved by the North West-Liverpool East Research Ethics Committee. Results will be published in peer-reviewed journals.

**Trial registration number:**

ISRCTN35717198

Strengths and limitations of this studyThe Investigating Concurrent Approach Bias Modification Training and Transcranial Direct Current Stimulation in Binge Eating Disorder (ICARUS) study is the first randomised controlled feasibility trial of multi-session transcranial direct current stimulation (tDCS) combined with cognitive bias modification training (CBM) for adults with binge eating disorder (BED).ICARUS will compare (tDCS+CBM) versus (sham tDCS+CBM) and a wait-list control group.ICARUS is designed to answer questions about the efficacy of the treatments tested.Results would need to be replicated in a larger trial before recommendations for tDCS+CBM as a treatment adjunct for patients receiving outpatient treatment for BED can be made.

## Introduction

Binge eating disorder (BED) is the most prevalent eating disorder (ED) worldwide, with 1%–3% of the general population meeting diagnostic criteria.^1 2^ Binge eating is a core symptom, characterised by consumption of large amounts of food, a sense of loss of control and significant distress. Nearly 80% of those with lifetime BED have a comorbid psychiatric disorder, such as mood, anxiety, substance use disorders or another ED.^2^ Due to the lack of compensatory behaviours (eg, vomiting, excessive exercising), BED is often accompanied by, or leads to, obesity and associated physical complications.^3 4^ In the general population, approximately 30%–42% of people with BED are obese.^2 5 6^ Around 30% of treatment-seeking obese people^7–9^ and up to 47% of bariatric surgery candidates have full or partial BED.^1 10 11^ While BED itself has considerable individual and societal costs,^12^ the combination of BED and obesity is associated with more severe obesity, greater medical and psychiatric comorbidity, greater functional impairment and perinatal complications.^12–15^ Treatments for BED and obesity are sub-optimally effective, with cognitive behavioural therapy (CBT)^16^ and some medications^17^ reducing binge eating and related psychopathology,^1^ and approximately 50%–60% of patients achieving abstinence from bingeing at the end of treatment^18^ with some sustained cessation at follow-up.^19^ However, drop-out rates in established BED treatments reach 12%–34%, and 30%–50% of BED patients relapse in long-term follow-ups,^20–22^ indicating that a substantial proportion do not maintain binge eating remission. Lisdexamfetamine^23^ and topiramate^24^ also reduce weight in the short-term but have considerable side effects,^25^ and their longer term efficacy is uncertain. Thus, there is a need for novel treatment developments.

The aetiology of BED is widely seen as multi-factorial. Emerging neurobiological models emphasise both the role of stress in the onset and maintenance of the disorder,^26 27^ and the development of addiction-like features; craving, tolerance and binge escalation over time,^28 29^ impulsivity and compulsivity, alterations in executive function and attention^30^ and reward-related decision-making.^31^

On encountering images of high-calorie food, BED patients report enhanced reward sensitivity and exhibit stronger medial orbitofrontal cortex responses compared with healthy controls and participants with bulimia nervosa (BN).^32^ In individuals with obesity, who may or may not have BED, activation in the ventral striatum (part of the reward system) has been found to be higher compared with normal-weight controls,^33^ in tandem with a more pronounced approach bias towards appetising food images,^34 35^ leading to greater likelihood of consumption. Furthermore, poor reward-related decision-making behaviour may be a maintaining factor in obesity.^36^ Converging data using different methodologies, such as brain imaging, eye tracking and behavioural test paradigms^37^ have found that patients with BED demonstrate a higher arousal rate in response to food stimuli, a concurrent motor plan to start eating, a higher reward sensitivity and greater inhibitory deficits as compared with individuals without BED.^32 38 39^ Those with obesity and BED (compared with obesity alone) have demonstrated that their attentional bias to food images held higher motivational value,^40^ and responded more to high calorie food images in sites of cognitive planning of motor movements, driven by emotions, which may reflect impulsive tendencies in the face of a binge-eating trigger. This tendency to approach and consume palatable food items may thus be compounded by a greater sensitivity to reward and a decreased capacity to inhibit action tendencies. This is corroborated by the recent finding that individuals with BED or BN show higher food cue reactivity (increased cravings) when exposed to visual food cues compared with healthy controls.^41^ Such accumulating evidence of BED as a unique diagnostic group situates it as a distinct phenotype within the obesity spectrum that is characterised by increased impulsivity.^42^

Conventional treatments of BED, such as CBT may not be best suited to target highly automatic cognitive processes that occur at an early stage in information processing and that are considered to contribute to food craving and associated maladaptive cognitions/behaviours. Two ‘brain-directed’ treatments may provide an avenue for modifying these processes: approach bias modification training (ABM) and transcranial direct current stimulation (tDCS).

ABM is a form of cognitive bias modification training (CBM) that aims to retrain approach bias tendencies (reach out towards) into avoidance ones (move away from)^43^ regarding stimuli such as appetitive cues. Participants are systematically trained to show an avoidance movement in response to illness-related rewarding stimuli (eg, food or alcohol) on a computer screen. ABM techniques have shown potential in several pilot and large-scale randomised controlled studies to treat alcohol^44^ and tobacco^45^ addictions, and to reduce consumption of cannabis^46^ and unhealthy foods.^47 48^ ABM has also yielded promising results in people with high levels of food craving and in bulimic EDs, including BED.^49 50^ However, mixed results in empirical studies across these domains^51 52^ raise methodological issues in ABM studies to date, such as low statistical power and suboptimal choice (or absence) of control groups^53^ and administration of single versus multiple training sessions.

tDCS is a form of non-invasive brain stimulation (NIBS) that has been used as a treatment adjunct for a range of psychiatric disorders, such as depression, schizophrenia and addictions.^54–56^ Preliminary evidence suggests that tDCS and other forms of NIBS are promising tools to reduce food cravings, ED symptoms and body weight in bulimic EDs, including BED, and obesity.^57^ Additionally, some studies indicate that NIBS may reduce depression/stress levels and improve reward-based decision-making in ED patients.^58^ A frequent stimulation target is the dorsolateral prefrontal cortex (dlPFC) which plays a major role in cognitive-inhibition, emotion regulation and reward processing.^58–61^ Although precise mechanisms of action of tDCS have yet to be understood, a key hypothesis in relation to BED is that enhancing dlPFC activity via tDCS alters the reward-cognition balance towards facilitation of cognitive control and suppression of reward-related mechanisms driving food craving/overeating.^62^

If given concurrently (ie, ‘online training’), NIBS is reported to boost the effects of cognitive training on the reduction of cognitive biases and the improvement of response inhibition.^63^ NIBS may enhance synaptic strength in neuronal pathways activated by cognitive training, amplifying effects of training and thus cognitive bias modification efficacy.^64^ As the effectiveness of tDCS may thus be improved by pairing administration with a cognitive task inducing activity in the target brain region,^65–67^ such combined treatment interventions have been investigated among alcohol dependent inpatients (ABM and tDCS),^68^ and to enhance inhibitory control related to food consumption (Go/No-Go Task and tDCS).^65^ The insignificant findings from these studies warrant commentary that to date, studies that have found positive effects of tDCS have either included obese participants or have had multi-session protocols.^65 69–71^ As this study incorporates both aspects, it is optimally designed to yield significant results.

In light of both the individual and societal burden incurred by the rising prevalence of BED and obesity, research interventions informing treatments that lead to stable and long-lasting remission are of critical importance, and novel therapies may play a role in serving as adjuncts to treatment as usual (TAU), to enhance improvement in clinical outcomes obtained from engaging with ED treatment services. This research trial is the first to combine two promising novel intervention strategies in an integrated treatment and will yield important findings to shape future clinical trials. The intervention conditions of this feasibility study will involve six sessions of concurrent ABM and real or sham tDCS over 3 weeks, and will assess participant acceptability and dropout rates at this treatment frequency and duration. Additionally, the frequency of participants’ ED symptoms and other outcomes related to general psychopathology and neurocognition will be measured before and after the study interventions to assess treatment success. In summary, this proof-of-concept and feasibility study will establish the utility of concurrent ABM+real tDCS in improving clinical outcomes in participants with BED, compared with ABM+sham tDCS, and a wait-list control group.

## Study aims

In line with established recommendations for outcomes of feasibility trials,^72^ which at present are supported by the National Institute for Health Research, the primary aim is to assess the feasibility of using concurrent ABM+real tDCS compared with concurrent ABM+sham tDCS as a potential adjunct to TAU in this patient population, and acquire key information to inform the development of a large-scale RCT.

The specific objectives of the proposed feasibility study are to:

Establish the feasibility of conducting a large-scale RCT of ABM+tDCS in patients with BED by assessing recruitment, attendance and retention rates.Determine the practicality of administering both ABM and tDCS simultaneously.Determine the best instruments for measuring outcomes in a full trial by examining the quality, completeness and variability in the data.Estimate the treatment effect sizes and SD for outcome measures to inform the sample size calculation for a large-scale RCT.Evaluate whether the treatment is operating as it is designed by analysing process measures, such as within-session Visual Analogue Scales (VAS) of key ED symptoms.Determine whether patients with BED evaluate concurrent ABM+tDCS as acceptable and credible.Obtain information about patients’ willingness to undergo random allocation to ABM paired with either real or sham tDCS administration, or the wait-list control condition.

A secondary aim is to investigate the potential efficacy of concurrent delivery of both forms of treatment on BED.

This will involve evaluating if:

Concurrent sessions of ABM+real tDCS are superior to ABM+sham tDCS and to wait-list control in terms of frequency of objective binge eating episodes, food cue reactivity, food craving, food intake, ED psychopathology and mood.Concurrent ABM+tDCS is superior to the two other conditions in having an effect on the targeted neurocognitive mechanism (approach bias for high calorie food) and related neurocognitive parameters (ie, impulsivity, delayed gratification, emotional regulation).Concurrent ABM and sham tDCS is superior to the wait-list control in eliciting therapeutic effects on the aforementioned clinical outcomes and neurocognitive mechanisms, yet demonstrates an efficacy level below that of concurrent ABM and real tDCS.

## Methods and analysis

This study protocol has been written according to the Standard Protocol Items for Randomised Trials statement^73^ and the Consolidated Standards of Reporting Trials (CONSORT) 2010 statement.^72^

### Study design

The Investigating Concurrent Approach Bias Modification Training and Transcranial Direct Current Stimulation in Binge Eating Disorder (ICARUS) trial is an exploratory randomised controlled feasibility trial with three parallel treatment conditions; ABM+real tDCS, ABM+sham tDCS and wait-list control. All participants across the two intervention groups will receive a treatment protocol of six sessions of ABM+real/sham tDCS conducted over 3 weeks. The comparator groups of a wait-list control and ABM+sham tDCS are necessary to evaluate the potential effect of real versus sham tDCS in participants with BED. The wait-list control group will be examined at the same time points to control for the possibility that improvements in the intervention groups are simply due to regression to the mean, spontaneous remission or other non-specific time effects. Any participants who are engaging in treatment for their ED will continue with TAU, and thus this selection of comparators is deemed acceptable. Within treatment session measures will involve VAS evaluating mood, stress and ED symptoms. Assessments will be conducted three times during the study; at baseline, post-treatment (week 3) and at follow-up (week 7).

### Participants

Inclusion criteria entail: (1) male and female community-dwelling adults (aged 18–70), (2) overweight or obese according to WHO criteria (body mass index (BMI) ≥25 kg/m^2^),^74^ (3) a diagnosis of full-syndrome or sub-threshold BED according to the Diagnostic and Statistical Manual (DSM)-5^75^, (4) fluency in English, (5) normal or corrected to normal vision.

Exclusion criteria entail: (1) all known contraindications to tDCS^76^; (2) pregnancy; (3) a current significant/unstable medical or psychiatric disorder needing acute treatment in its own right; (4) a lifetime diagnosis of substance dependence, psychosis, bipolar disorder or borderline personality disorder; (5) taking psychotropic medication other than a stable dosage of selective serotonin reuptake inhibitors for at least 14 days prior to study enrolment; (6) allergies to any of the foods presented in the study; (7) smoking >10 cigarettes per day; (8) drinking >3–4 units (men) or 2–3 units (women) of alcohol per day. In line with the CONSORT guidelines,^77 78^ we will record the number and reasons for any participants we must exclude, or any who decline consent or withdraw from the study.

### Sample size

As ICARUS is a feasibility study, an a priori sample size calculation is not necessary. Rather, its aim is to provide effect sizes on which future large-scale studies can be powered. Total study sample sizes of n=24 to n=50 have been recommended for feasibility trials with a primary outcome measured on a continuous scale, mainly because estimates of the SD for normally distributed variables tend to stabilise around this size.^79 80^ We have chosen a target end study sample size of n=60, (ie, exceeds the upper end recommended for feasibility trials). However, assuming the attrition to follow-up rate is a=0.10 (as found in previous ED trials^81 82^) and applying an attrition correction factor of 1/(1-a), we will recruit an actual sample size of 66, that is, 22 participants per group.

### Randomisation

After the baseline assessment, participants will be allocated to one of three conditions at random to receive six sessions of either concurrent ABM+real tDCS or ABM+sham tDCS, or no intervention in the wait-list control condition. As a proportion of participants recruited from an outpatient ED clinic will be on a waiting list to receive treatment at the time of enrolment in this study and may commence treatment shortly after study enrolment, this study will not seek to balance groups in terms of therapy engagement or medication usage. Participants in the wait-list control group will be offered the opportunity to receive ABM+real tDCS after the end of the follow-up. Participants will be individually randomised on a 1:1:1 ratio to the intervention or control groups in equal numbers. The generation and implementation of the randomisation sequence will be conducted independently from the trial team through a randomisation administrator who is not involved in any recruitment or research activity related to the ICARUS study. Online randomisation software (Sealed Envelope, London, UK) will be used for this purpose. On participant enrolment, the researcher will contact the randomisation administrator, who will inform this researcher in charge of carrying out the intervention of the participant's allocation via phone, email or paper letter.

### Blinding

Double blinding is implemented only for the intervention group cohorts of the trial. The research assessor will remain blind to each participant’s tDCS assignment within the two intervention conditions until the study data collection phase has been completed. This double blinding protocol will be ensured via administration of the tDCS (NeuroConn DC-STIMULATOR PLUS) using ‘study mode’. This involves a five-digit numerical code unique to each patient will be inputted into the device prior to the participant’s testing session, that will initialise either sham or real (active) stimulation. The tDCS administrator and participants will remain blind to tDCS stimulation type throughout the study. Set-up of the randomisation codes and programming of the tDCS device will be performed by an investigator not involved in the trial. To assess blinding success, each participant and the researcher will be asked to guess the treatment allocation at the end of the six treatment sessions and to indicate how certain they are of this guess. The study group allocation will be revealed to the participant after their follow-up assessment by the study randomisation administrator. In the event of a reported change in a participant’s medication, or a new clinical diagnosis made during their study participation, the early unblinding of study condition for an intervention group participant will be permissible. The trial database will be maintained ‘blind’ until the point of study data analyses.

### Recruitment

The study will take place at the Institute of Psychiatry, Psychology and Neuroscience (IoPPN), King’s College London (KCL), UK. Participants will be recruited from the Eating Disorders Service at the South London and Maudsley NHS Foundation Trust, from the KCL research recruitment webpage and social media account, and via posters placed on notice boards on KCL campuses. Participants who have previously taken part in research at the KCL Eating Disorders Unit and who have consented to be informed of future studies may also be contacted. The ICARUS study will also be advertised on the Beat (National Eating Disorders Association) website, callforparticipants.com and www.mqmentalhealth.org. Potential participants will receive written and verbal study information and will be screened for eligibility. Eligible participants will provide informed written consent for study participation as a prerequisite for enrolment (online supplementary appendices A and B).

10.1136/bmjopen-2019-030023.supp1Supplementary data

### Procedure

Figure 1 illustrates the timeline of the study procedures. All participants will partake in assessments at each of the three measurement points; baseline, post-treatment and follow-up. Each assessment will comprise of an in-person study visit with tasks and measures, and online/hardcopy questionnaires and scales to be completed at home by the participant within 36 hours following the study visit. Table 1 details the tasks and measures allocated to each assessment and training visit. After the baseline assessment, participants are randomised to one of three groups: (1) ABM+real tDCS, (2) ABM+sham tDCS or a wait-list control group. Participants allocated to an intervention group will be offered six sessions of ABM+real/sham tDCS across 3 weeks. All study participants may receive TAU, for example, if they are currently engaged in outpatient treatment for their ED. The control group will not receive any study intervention, and any participants receiving outpatient services treatment for their ED will continue TAU during this 3 week period. The post-treatment assessment will be conducted on all participants after the sixth (final) session of ABM+real/sham tDCS for the intervention groups, and 3 weeks after the baseline assessment for the control group. The follow-up assessment will be conducted 28 days after the end of treatment, that is, 7 weeks post-randomisation. A follow-up period is included because if the effects of the intervention result from increased neuroplasticity, behavioural changes may need time to emerge. Assessing the longevity of favourable clinical outcomes beyond the treatment period is also relevant to the objectives of this feasibility study. The researcher conducting the assessment and testing sessions will remain blind to the study condition of intervention group participants until the study data collection period is completed.

**Figure 1 F1:**
[figure not shown]
Study procedure. The three assessment time points are baseline, post-assessment and follow-up. ABM, approach bias modification training; CG, wait-list control group; IG1, intervention group 1; IG2, intervention group 2; tDCS, transcranial direct current stimulation.

**Table 1 T1:** Study schedule of measurement and testing time points

Approximate time since baseline	Screening of potential participants	Baseline assessment (all participants)	Training: six sessions of ABM+real tDCS 0–3 weeks	Training: six sessions of ABM+sham tDCS 0–3 weeks	Post- assessment (all participants 3 weeks	Follow-up (all participants) 7 weeks
Informed consent		X				
EDDS, SCID-I	X					
tDCS safety screening	X					
Demographic information		X				
EDE-Q^83^		X			X	X
Inhibitory control tasks; Go/No-Go task^105^, SST^107^		X			X	X
Delay discounting task with money and food^103^		X			X	X
Food-related tasks; food choice task^88^, FCT, bogus taste test^102^		X			X	
Approach bias assessment tasks; F-AAT^85^, SRC^87^		X			X	X
Questionnaires and scales (incl. at home); EDRSQ,^119^ FCQ-T-r,^94^ PFS,^95^ YFAS 2.0,^96^ ERQ,^108^ PANAS,^109^ BIS-11,^120^ CIA,^121^ DGI,^104^ DASS-21^110^		X			X	X
Pre-(tDCS+ABM) measures: Multiple VAS, blood pressure, pulse			X	X		
Real or sham tDCS to dLPFC			X	X		
Approach bias modification training			X	X		
Post-(tDCS+ABM) measures: Multiple VAS, blood pressure, pulse			X	X		
Tolerance, discomfort and side effects			X	X		
Acceptability questionnaire						X
Blinding assessment questionnaire						X

ABM, approach bias modification training; BIS-11, Barrett Impulsiveness Scale; CIA, Clinical Impairment Assessment; DASS-21, Depression, Anxiety and Stress Scale; DGI, Delayed Gratification Inventory; dLPFC, dorsolateral prefrontal cortex; EDDS, Eating Disorder Diagnostic Screen; EDE-Q, Eating Disorder Examination; EDRSQ, Eating Disorder Recovery Self Efficacy Questionnaire; ERQ, Emotion Regulation Questionnaire; F-AAT, Food Approach-Avoidance Task; FCQ-T-r, Food Cravings Questionnaire Trait Version–reduced; FCT, Food Challenge Task; PANAS, Positive and Negative Affect Schedule; PFS, the 21-item Power of Food Scale; SCID-I, Structured Clinical Interview for Diagnostic and Statistical Manual (DSM) Axis I Disorders; SRC, Stimulus Response Compatibility Task; SST, Stop Signal Task; tDCS, transcranial direct current stimulation; VAS, Visual Analogue Scale; YFAS 2.0, Yale Food Addiction Scale Version 2.0.

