#### Intervention/service related outcomes

Feasibility outcomes include recruitment, attendance and retention rates, and acceptability of treatment by participants. Patients’ acceptance of study interventions will be assessed by measuring treatment dropout rates and via the treatment tolerance and acceptability questionnaires. An interview assessment of treatment experience will be conducted with 20 participants after the follow-up is completed. Ten participants from each intervention group will be invited to provide feedback on their initial expectations and experiences of the ABM+real/sham tDCS treatments, perceived strengths and weaknesses of the treatment they received, and suggestions for improvements in procedures. Interviews will be recorded, transcribed and analysed using thematic analysis. This will allow future studies to consider patients’ feedback in the development of research and clinical protocols of concurrent ABM and tDCS.

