### Ethics and safety aspects

This trial will be conducted in compliance with the study protocol, the Declaration of Helsinki, the principles of good clinical practice (ICH-E6 guideline), the ICH-E8 guideline and the principles of good clinical practice and in accordance with all applicable regulatory requirements including but not limited to the UK policy framework for health and social care research. All participants will be asked by the study researcher to provide written informed consent prior to enrolment. Participants who are at-risk for adverse side effects^76^ will be excluded from the study at the screening stage (ie, such as those with pregnancy or epilepsy). Current safety parameters of tDCS administration regarding voltage amplitude and duration of brain stimulation sessions will be adhered to. Participants have the option to withdraw immediately and terminate their participation in the study if they experience discomfort during tDCS administration, or if they wish to terminate their participation for any other reason that they may or may not wish to disclose. After each training session, participants will complete the tolerance, discomfort and side effects questionnaire to report any adverse effects of the intervention training session. The researcher will record this description of any reported adverse effects, and record the severity and duration of symptoms and how the adverse effect was managed at the following training session. If a participant reports a new clinical diagnosis or change in medication during their involvement in the study, a decision regarding their continued participation in the study will be made by the research team and withdrawal of the participant may be deemed necessary. Standard KCL insurance and NHS indemnity arrangements apply to this study. To promote study adherence, on completion of the follow-up assessment, each participant will be reimbursed for their time, efforts and travel (£60 for assessments and up to £60 for travel expenses). Additionally, participants in the wait-list control group will be offered the opportunity to receive 6 sessions of ABM+tDCS after the follow-up.

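### The direct acceptability rating is scheduled only at week 7, so those lost earlier give none, and interviews may take place after allocation is disclosed

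*Protocol article*

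**What the plan says.** Under Study aims, one specific objective is to "Determine whether patients with BED evaluate concurrent ABM+tDCS as acceptable and credible". The section on intervention and service related outcomes makes this a feasibility outcome: "Feasibility outcomes include recruitment, attendance and retention rates, and acceptability of treatment by participants". It names the measures: "acceptance of study interventions will be assessed by measuring treatment dropout rates and via the treatment tolerance and acceptability questionnaires".

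The timing of each source is as follows.

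- **Acceptability questionnaire.** In Table 1 the row "Acceptability questionnaire" is marked only under follow-up at 7 weeks. It has no mark under the training sessions or the week-3 post-assessment. Procedure places follow-up 28 days after the end of treatment.
- **Tolerance form.** Ethics and safety aspects states: "After each training session, participants will complete the tolerance, discomfort and side effects questionnaire". Table 1 agrees for both intervention groups.
- **Interviews.** These come last: "An interview assessment of treatment experience will be conducted with 20 participants after the follow-up is completed". The same section splits them equally between the two arms and says nothing about including people who stopped early.
- **Disclosure.** Under Blinding, "The study group allocation will be revealed to the participant" once the follow-up assessment is done.

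The Participants section adds that numbers of withdrawals and the reasons for them will be recorded.

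**The concern.** The two instruments that ask participants to evaluate the treatment as a whole, the questionnaire and the interview, both sit at or after week 7. People who found the treatment hard to accept are plausibly the ones most likely to be gone by then. Within session safety procedures and Ethics and safety aspects both offer a participant who has discomfort during stimulation an exit from the study, not only from the sessions. Data analysis keeps what was already obtained from those who discontinue, but under the Table 1 schedule no acceptability form would yet exist to keep. The missing ratings may therefore depend on acceptability itself, and the observed rating may be too favourable.

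The second issue is hindsight. The interviews ask about initial expectations and about the strengths and weaknesses of the treatment received. A participant who has just learned that the stimulation was sham may answer differently from one who has not.

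The result feeds the decision on whether and how to run a large trial, so both effects bear on what this study is for.

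**Working it through.** **Inputs from the protocol article**

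- 66 participants, 22 per group (Sample size), allocated 1:1:1 (Randomisation). The two intervention groups hold 2 × 22 = 44.
- Planned attrition to follow-up: a = 0.10 (Sample size).
- Dropout from other treatments: 17–30% for CBT in BED (Discussion) and 12–34% for established BED treatments (Introduction). These are not forecasts for this trial and serve only as a range.

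**The plan's own figure.** 60 / (1 − 0.10) = 66.7, against the stated 66. Per group, 20 / 0.9 = 22.2, against 22. The figure is reproduced to within rounding, and nothing below depends on the difference.

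**Step 1: direct ratings missing at week 7.** Expected number = 44 × a, assuming the rate applies equally to the intervention groups.

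| Attrition | Missing of 44 |
|---|---|
| 10% (planned) | 4.4 |
| 12% | 5.3 |
| 17% | 7.5 |
| 30% | 13.2 |
| 34% | 15.0 |

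**Step 2: bounds on acceptability over all 44.** Let p be the proportion of responders who call the treatment acceptable. The overall proportion lies between p(1 − a), if no missing participant would agree, and p(1 − a) + a, if all would. With p = 0.90 (assumed):

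- a = 0.10: 0.81 to 0.91
- a = 0.17: 0.75 to 0.92
- a = 0.30: 0.63 to 0.93

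**Step 3: illustration of the upward bias.** Let q be the proportion of missing participants who would call the treatment acceptable, assumed to be 0.20 to 0.50. Overall = (1 − a) × 0.90 + a × q.

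- a = 0.10: 0.81 + 0.02 = 0.83, to 0.81 + 0.05 = 0.86. The responders' figure is 4–7 points too high.
- a = 0.17: 0.747 + 0.034 = 0.78, to 0.747 + 0.085 = 0.83. It is 7–12 points too high.
- a = 0.30: 0.63 + 0.06 = 0.69, to 0.63 + 0.15 = 0.78. It is 12–21 points too high.

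**Step 4: order of interview and disclosure.** No arithmetic applies. Blinding puts disclosure after the participant's follow-up assessment. Intervention/service related outcomes puts the interview after follow-up is completed. Both events share the same earliest time and no text orders them. The questionnaire is different: it is scheduled at the follow-up visit, so it precedes scheduled disclosure.

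**The case against.** A reader might infer that acceptability is a primary outcome, that it is measured only at week 7 and by interview, that dropouts are not heard, and that the comparison of real with sham experience is unblinded. The documents do not support this stronger reading, for five reasons.

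- The article counts dropout rates and the tolerance questionnaire as measures of acceptance. Tolerance is recorded after every session, so early leavers contribute up to their last one.
- Reasons for withdrawal are to be recorded.
- Stopping sessions is not the same as missing week 7. Procedure schedules all participants at every assessment, an intent-to-treat analysis is planned, and nothing bars someone who stopped sessions from attending.
- Acceptability serves the primary aim but is not itself labelled primary.
- No formal comparison of interviews between real and sham is stated; the analysis is thematic. The questionnaire rating comes before scheduled disclosure.

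It can also be said that interview sampling and sequence are details a full protocol may settle, and that at 10% attrition the assumed bias of 4–7 points is smaller than the sampling error. The 95% half-width for 90% of 40 responders is 1.96 × √(0.9 × 0.1 / 40), or about 9 points. Finally, the week-7 mark may be a slip in the table: the adjacent blinding questionnaire is also marked only at week 7, whereas the Blinding section asks for the guess at the end of the six sessions.

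Most of this stands and limits the point. It does not remove it. The tolerance form is described as a report of adverse effects, not as an evaluation of acceptability or credibility. Participants may withhold a reason for leaving. A bias is not made harmless by being smaller than the sampling error, and it can be reduced here at little cost. If the table mark is a slip, it needs correcting for that reason.

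**Conclusion.** The point holds in a limited form. As scheduled, the direct acceptability rating comes only from people retained to week 7, and the order of interview and disclosure is left open. At the planned attrition about 4 of 44 intervention participants would give no direct rating. With 90% acceptability among responders, the overall figure is then bounded by 81% and 91%, and the upward bias is 4–7 points if 20–50% of those missing would agree. At 30% attrition the bias would be 12–21 points, but that rate is borrowed from CBT and may not apply to a 3-week intervention. The 90% and the 20–50% are assumptions, and the direction of the bias rests on those who leave being less favourable.

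Knowledge of allocation at interview is a possibility, not an established fact. The sample size and the clinical outcome analyses are unaffected. The change is worth making because the objective is explicit and the cost is small.

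**What to change.** 1. Keep the week-7 acceptability questionnaire, and also give it to both intervention groups at the existing week-3 post-assessment. Offer it at the point of stopping to anyone who discontinues and agrees to complete it. Amend Table 1 to match.
2. State that each interview takes place before that participant's allocation is disclosed.
3. Invite some people who stopped early among the 20 interviewees.
4. Report the ratings by group alongside the number missing out of all allocated to intervention, next to dropout, tolerance and recorded reasons for withdrawal.

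The cost is one short form repeated, at an existing visit or through the online or paper route already in use, and slightly later disclosure for interviewees. No new visit or staff is needed.
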